### Sensory-related sleep risks for VPIs during NICU hospitalization

Sleep undergoes progressive changes during intrauterine and extrauterine life in preterm infants. These changes depend heavily on GA [5, 9]. After preterm birth, infants are exposed to the NICU environment, which includes various sources of stress like excessive noises, prolonged high-intensity lighting, and frequent invasive procedures for neonates [10]. Moreover, hospitalized VPIs usually face long periods substantially lacking organized, cyclic, and multimodal stimulation across the senses, which, in general, the human fetus experiences in the uterus [9–12]. Hence, it can be deduced that sensory exposure and abatement will contribute to sleep deprivation and disorder risk in VPIs during NICU hospitalization.

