## Methods/design

### Study design and setting

This study was designed as a prospective, evaluator-blinded, randomized crossover trial, in accordance with the Standard Protocol Items: Recommendations for Interventional Trials guidelines. This study is conducted in the neonatology department of Shanghai Children’s Medical Center, a pediatric tertiary teaching hospital, and the National Children’s Medical Center in China. The study protocol has been approved by the Hospital Research Ethics Committee (approval number: SCMCIRB-K2021086-1) and is registered in the Chinese Clinical Trial Registry (Registry Number: ChiCTR2200059099).

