### Randomization and allocation

The study participants will be randomly assigned to group A or B with a distribution ratio of 1:1. A statistician has prepared a computer-generated randomization list with variable block sizes. The random allocation will be concealed in serially numbered, opaque, and sealed envelopes prepared for the site.

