### Interventions with participants and investigation equipment

Participants will receive two types of care—“standard care” and “standard care plus multisensory stimulation bundles”—randomly for two consecutive weeks each (see schedule of enrollment, interventions, and assessments in Fig. 2). Thus, every participant will receive the tested intervention. The difference between the groups will only be the order in which they receive the intervention. Furthermore, all healthcare providers will receive detailed training on the study process before the study commences. To ensure precise and standard sensory stimulations, we will provide the multisensory stimulation bundles using the multisensory stimulation-supported device. The device application’s standard operating procedure (SOP) has been developed. All healthcare providers involved in VPI care will be trained to apply the device and standard care through presentations and bedside demonstrations prior to the start of the study, ensuring intervention homogeneity.

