#### Primary outcome

The primary endpoint of this study is sleep efficiency, which is defined as the average proportion of sleep time for 7 days at weeks 2 and 4 (see Fig. 2). In this study, sleep is defined as three consecutive minutes with lower-extremity movement below the threshold. It is measured using an actigraphy watch (model: Actiwatch-2). Actigraphy is a reliable and valid method for continuously recording limb movements and transferring sleep parameters [31, 32]. Data from the Sleep Watch Actigraph will be coded into sleep and wake states at 1-min intervals using Action 4 research-level software (Ambulatory Monitoring, Inc, Ardsley, New York), compatible with the actigraphy watch. Sleep/wake measures will be extracted from actigraphy data by one investigator who is blind to the infants’ assigned groups. The actigraphy watch weighs 27 grams. Previous observations made at the study institution have shown that the device has minimal impact on infants’ activities. To further minimize its impact on the activities of preterm infants, the researcher will uniformly place the watch on the infant’s thigh.

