### Data analysis

The baseline characteristics of the samples will be presented as *N* (%) for categorical variables and mean ± SD or median (IQR) for quantitative variables, depending on the data distribution. The primary and secondary outcomes will be analyzed using a linear mixed-effect model with “intervention” as a between-subjects factor and “time” as a within-subjects factor. The primary outcome (sleep efficiency) will be evaluated at timing points of week 2 (T2 timing point) and week 4 (T4 timing point) after randomization during the hospitalization. We compared the mean difference between primary and secondary outcomes as follows: group A (T2) vs. group B (T4) and group A (T4) vs. group B (T2). Moreover, every participant will receive the investigated intervention, and the difference between the groups will be the order in which they receive it. Therefore, no statistical difference would exist between groups during the follow-up period. Hence, we will only conduct the statistical description of the follow-up indicators. No statistical test will be prespecified regarding the follow-up indicators in this study. The intention-to-treat analysis will be used for missing values during each data collection. Although cases of missing data are expected to be rare, multiple imputations assuming random missing data will be used for this study. SPSS software version 24.0 (IBM Corp., Armonk, NY, USA) will be used for data analysis. Two-tailed *p*-values < 0.05 will be considered indicative of statistical significance.

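### Both comparisons listed in the Data analysis section set infants on the same care against each other two weeks apart, so the bundle effect cancels from each, and the mixed model named beside them does not clearly repair this

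*Protocol article*

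**What the plan says.** The Study design and setting section describes a "prospective, evaluator-blinded, randomized crossover trial". Infants are "randomly assigned to group A or B with a distribution ratio of 1:1" (Randomization and allocation) and receive the two types of care "randomly for two consecutive weeks each" (Interventions with participants and investigation equipment). That last section adds: "The difference between the groups will only be the order in which they receive the intervention".

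Sleep efficiency, the primary endpoint, is "defined as the average proportion of sleep time for 7 days at weeks 2 and 4" (Primary outcome). The Data analysis section places the evaluations at "week 2 (T2 timing point) and week 4 (T4 timing point) after randomization". T2 therefore closes the first care period and T4 the second.

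The Data analysis section names a linear mixed-effect model with intervention between subjects and time within subjects. It then gives the comparisons of means for the primary and secondary outcomes as "group A (T2) vs. group B (T4) and group A (T4) vs. group B (T2".

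**The concern.** When two groups differ only in order, group A in its first period and group B in its second are on the same care. Group A in its second period and group B in its first are both on the other care. Each listed pair is therefore standard against standard, or bundle against bundle, in different infants measured two weeks apart.

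The first objective is the effect of the bundle on sleep efficiency, and neither pair measures it. If the pairs were taken as the result, a bundle that works could appear to do nothing, and ordinary maturation could appear as a finding. Some age effect is to be expected: on the progressive changes in preterm sleep, the background says "These changes depend heavily on GA".

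**Working it through.** **Inputs from the protocol.** Planned difference 0.04, SD 0.05, two-sided 5%, power 90%, 36 infants (18 per group), 40 after 10% dropout (Sample size calculation). The within-infant correlation and the two-week age effect are not given and are assumed below.

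**The plan's own figure.** For a 2×2 crossover with within-person SD 0.05, N = 2 × [0.05 × (1.960 + 1.282) / 0.04]² = 32.8. The t-based version gives power 0.892 at 34 and 0.909 at 36, so 36 is the even number that reaches 90%, and 36 / 0.90 = 40. The figure is reproduced if 0.05, which the protocol calls inter-person, serves as the within-person SD. A comparison of two independent groups with SD 0.05 would need 33 per group. The sample size therefore fits a within-infant crossover contrast, which the listed pairs are not.

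**Cell means.** Let m be the mean on standard care in period 1, τ the bundle effect, π the period (age) effect and λ any carryover from the bundle into the next period.

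| | T2 | T4 |
|---|---|---|
| A, standard care first | m | m + τ + π |
| B, bundle first | m + τ | m + π + λ |

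- A(T2) − B(T4) = −π − λ
- A(T4) − B(T2) = +π

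If A has the bundle first, the two differences are −π and π + λ. In either case τ is absent from both, and λ enters only the pair on standard care. The flow figure is not needed to establish this.

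**Contrasts that do contain τ** (A on standard care first):

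- ½[(A T4 − A T2) − (B T4 − B T2)] = ½[(τ + π) − (π + λ − τ)] = τ − λ/2
- A against B at the same week: −τ at T2 and τ − λ at T4

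**The mixed model.** If the between-subjects factor is the group, its main effect averaged over the two periods is ½(2m + τ + π) − ½(2m + τ + π + λ) = −λ/2, again without τ. The bundle effect would appear through a group-by-time term, whose value is 2τ − λ, or if intervention were coded as the care received in each period. The section states neither.

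**Size.** For a listed pair, SE = 0.05 × √(2/18) = 0.0167. For the crossover contrast with assumed correlation 0.3, the SD of within-infant differences is 0.05 × √(2 × 0.7) = 0.0592, and SE = ½ × 0.0592 × √(2/18) = 0.00986. Two-sided t-tests on 34 degrees of freedom, with no carryover, give these rejection rates:

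| Bundle effect | Assumed age effect | Each listed pair | Crossover contrast |
|---|---|---|---|
| 0.04 | 0 | 5% | 97.6% |
| 0 | 0 | 5% | 5% |
| 0 | 0.02 | 21% | 5% |
| 0 | 0.04 | 65% | 5% |

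Simulation with 20,000 trials per row agrees. The rates for each pair do not depend on the correlation, because the two sides are different infants. Crossover power is 91% at correlation 0 and above 99% at 0.5.

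**The case against.** The strongest reply is that the pairs are not the whole plan. The same section names the mixed model first and does not call the pairs the primary test. With care received coded by period, or with a group-by-time term, that model would estimate the bundle effect with time adjusted. A reader might infer from the pairs alone that the trial is bound to miss its effect. The documents do not support that: it would hold only if the pairs, and not the model, decided the result. What remains is that the model is described with a between-subjects intervention, which does not suit a trial where every infant has both types of care, so it does not clearly correct the pairs.

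A drafting slip is also plausible. Pooled, A(T4) + B(T2) against A(T2) + B(T4) is exactly the valid crossover contrast, and these are the groupings listed. But the text sets the comparison inside each pair, and an analyst who followed it would test the wrong quantity.

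Third, the Control variables and covariates section lists postmenstrual age at sleep measurement. Adjusting for it could lower the age-driven rejection rates. It would not put τ back into the pairs, and the section ties use as a covariate to metrics on which the groups do not match.

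A reader might also infer a multiplicity failure from two comparisons with no rule for which decides. That detail is commonly left to an analysis plan, which is not shown here, and the question goes away once the sentence is replaced.

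**Conclusion.** The concern holds for the listed pairs. As written, neither comparison contains the bundle effect. This follows from the design alone, whichever group starts with the bundle and whatever the correlation or age effect. The mixed model beside them leaves the matter unclear and does not settle it.

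The sizes are illustrations. They rest on 18 per group, on 0.05 as the total SD at each time point, on no carryover and, for the crossover contrast, on an assumed correlation of 0.3. The 21% and 65% rest on assumed age effects of 0.02 and 0.04. The protocol supports age dependence but gives no magnitude, so a reader should not take 65% as the expected false-positive rate.

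**What to change.** Replace the sentence listing the pairs with one primary contrast, bundle minus standard care, estimated within infant as ½[(A T4 − A T2) − (B T4 − B T2)], with the sign set by which group has standard care first. Obtain it from the mixed model with care received in each period (a within-subject factor), period and sequence as fixed effects and infant as a random effect, tested once at two-sided 0.05. Any comparison at a single time should be group A against group B at the same week.

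The cost is one paragraph of analysis wording, with no new data and no additional infants. It should be settled before the outcome data are analysed.

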#### Secondary outcomes

Secondary study outcomes will include the following variables:Other sleep indicators: Sleep duration, fragmentation index, and amplitude of limb movement will also be obtained using the actigraphy watch (model: Actiwatch-2).Burdjalov Score: The Burdjalov Score is a scoring system used to evaluate the brain maturation of neonates. It is measured through aEEG examinations (CFM3000). It comprises four component variables: (1) presence or absence of “sleep–wake cycling,” (2) continuity of the brainwave record pattern, (3) recording bandwidth, and (4) lower-border amplitude (in μV) (see Table 1). Each variable will be independently evaluated, and each participant’s scores will be summed to determine the total score for each recording [33]. The minimum and maximum possible total scores are 0 and 13, respectively. A qualified physician will conduct bedside aEEG examinations, which involve continuous data collection over 4 h at baseline, week 2, and week 4 after randomization (see Fig. 2). Afterward, the physician will interpret the aEEG data to calculate the Burdjalov Score. During the aEEG examination, the room temperature will be maintained at 24–28°C, while unnecessary iatrogenic procedures on the infant will be minimized.The Griffiths Mental Development Scales (GMDS) with six subtests will be used to assess neurodevelopment in children aged 0–2 years [34, 35]. Each subtest measures a different development area: (A) locomotor, (B) personal–social, (C) hearing and language, (D) eye and hand coordination, (E) performance, and (F) practical reasoning. The mental age (MA) is derived by calculating the average raw scores of the six subtests. The corrected age (CA) is calculated as the difference between the examination and birth dates. The developmental quotient (DQ) is expressed as a mental ratio, i.e., DQ = (MA / CA) × 100. Finally, the total development quotient is represented by GQ, which represents the average value of all the development quotients [35]. The scale is culturally appropriate for Chinese children [35]. In this study, two physician research assistants with international GMDS qualifications will conduct GMDS assessments on study participants. Furthermore, the assessment process will be video-recorded for possible replay. Interrater measurement consistency will be obtained prior to the actual assessment of infants to reduce errors.Growth indicators at follow-up will include weight, length, and head circumference. Moreover, the research assistant will collect data when participants return for follow-up at 3, 6, and 12 months of CA.

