### Sample size calculation

In the previous pilot study conducted during October 2021 to February 2022, five participants in the intervention group vs five with matched characteristics in the control group were compared. The primary outcome (defined as sleep efficiency) was found to be 0.52 and 0.48 in the intervention and control group, respectively. The intervention effect size was estimated to be 0.04, and the inter-person standard deviation, 0.05. Considering a two-tailed significance level of 5% (α) and a test power of 90%, the required sample size is 36, with 18 in each group. Considering a dropout rate of 10%, 40 participants will be recruited for this study. In the past 5 years, the study setting received more than 100 VPIs every year, which means the sample size could be achieved in the planned time frame.

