## Discussion

In the last decade, research on sensory-based interventions has been highly emphasized. It has been requested that the procedure and impacts of the interventions show precise steps and be objectively measured during NICU hospitalization, particularly for very and extremely preterm infants [9, 25]. However, clinical staff or parents provide most primary sensory stimulation for infants in a busy neonatal care unit. Therefore, ensuring the sensory stimulation is provided with standard procedures, precise details, and proper doses of stimuli throughout NICU hospitalization [9, 23, 24] may be challenging. Directing this research toward addressing the clinical utilization gap is an urgent matter that needs to be resolved to advance clinical practice for highly preterm infants and improve their sleep and neurobehavioral outcomes.

The intervention protocol of this study differs from traditional interventions as it creates an infant care device that could produce a precise and consistent stimulation similar to the maternal tactile, auditory, posture, and visual effects for hospitalized preterm infants and VPIs. This study presents the first multisensory stimulation device that integrates a multimodal care bundle based on global guidelines and solid clinical evidence. Furthermore, simultaneously, this study will provide new perspectives on strategies for parent and infant reciprocal interaction that are critical for sleep and neurobehavioral development, particularly for NICUs that must limit the frequency of visits because of the COVID-19 pandemic.

The hypothesis of this study protocol is that preterm infants who receive the multisensory stimulation bundle protocol using the multisensory stimulation device will have improved sleep, early neurodevelopment outcomes, and growth development within the early period of infancy. Moreover, the study investigators will observe the safety, clinical feasibility, and applicability of this newly designed multisensory stimulation device. If the hypothesis is confirmed, the results could further generalize the implementation of protocols of multisensory stimulation bundles in NICUs and indicate that the device is an effective and low-cost measure to facilitate sleep and early neurodevelopment of hospitalized preterm neonates.

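### The primary endpoint gets a mixed model and two listed comparisons with no deciding test named, and neither listed comparison tests the bundle

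*Protocol article*

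**What the plan says.** The Primary outcome section names a single primary endpoint, sleep efficiency measured by actigraphy at weeks 2 and 4. The sample size rests on that endpoint alone: "Considering a two-tailed significance level of 5% (α) and a test power of 90" per cent, with "The intervention effect size was estimated to be 0.04, and the inter-person standard deviation, 0.05".

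The Data analysis section then gives two routes to a result.

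- A linear mixed model, with intervention described as a between-subjects factor and time as a within-subjects factor.
- A pair of comparisons: "We compared the mean difference between primary and secondary outcomes as follows: group A (T2) vs. group B (T4) and group A (T4) vs. group"; the sentence ends with the week 2 value of the second group.

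Both routes cover primary and secondary outcomes. One threshold is stated for everything: "Two-tailed *p*-values < 0.05 will be considered indicative of statistical significance". Only the follow-up indicators are taken out of testing.

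The secondary outcomes measured in hospital are the Burdjalov Score and three further watch measures: "Sleep duration, fragmentation index, and amplitude of limb movement will also be obtained using the actigraphy watch (model: Actiwatch-2").

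The section on interventions says that every infant receives both types of care and that the groups differ only in order. The Discussion states the hypothesis that treated infants "will have improved sleep, early neurodevelopment outcomes, and growth development within the early period of infancy", and continues: "If the hypothesis is confirmed, the results could further generalize the implementation of protocols of multisensory stimulation bundles in NICUs".

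**The concern.** The sample size spends the whole 5% on one test, but the analysis text does not identify that test. A reader cannot tell whether a model term, one listed comparison or both must be significant, or what follows if they disagree. If either comparison may be called significant at 0.05, the error rate on the primary endpoint exceeds the stated 5%.

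The second problem is what the comparisons measure. In a two-period crossover, group A in one period and group B in the other period are on the same treatment. The listed pairs therefore pick up change over time, not the effect of the bundle. Such change is to be expected: the Introduction says that preterm sleep changes progressively and depends heavily on gestational age, and postmenstrual age at measurement is a planned covariate. A result driven by two weeks of maturation could be reported as a bundle effect, or a real bundle effect could go unseen.

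**Working it through.** **Inputs.** From the Sample size calculation section: difference 0.04, SD 0.05, two-sided 5%, power 90%, 36 infants (18 per sequence), 40 after 10% dropout. Assumed, because the article does not give it: the correlation ρ between an infant's two sleep-efficiency values, taken from 0 to 0.8. Also assumed: normal data and no carry-over.

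**Step 1: the plan's own figure.** The SD of the within-infant difference is 0.05 × √(2(1 − ρ)), which is 0.0707 at ρ = 0.

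- Normal approximation: (0.0707 × (1.960 + 1.282) / 0.04)² = 32.8, so 33 infants.
- Two-sequence crossover t-test on N − 2 degrees of freedom: at N = 36 the noncentrality is 0.04 / (0.0707/√36) = 3.39 and power is 0.909. This is the smallest even N that reaches 90%.
- Dropout: 36 / 0.9 = 40.

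The stated 36 and 40 are therefore reproduced by one treatment contrast in a crossover. A comparison of two independent groups of 18 with the same inputs would have power of only about 0.64.

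**Step 2: error rate of the two listed comparisons.** Let D1 = A(T2) − B(T4) and D2 = A(T4) − B(T2), with σ the per-period SD. Each has variance 2σ²/18 and their covariance is 2ρσ²/18, so their correlation is ρ. With no treatment or period effect, the chance that at least one gives p < 0.05 is:

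| ρ (assumed) | Chance of at least one |
|---|---|
| 0 | 1 − 0.95² = 9.75% |
| 0.5 | 9.1% |
| 0.8 | 7.8% |

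Simulated t-tests with 18 per sequence agree: 9.9% at ρ = 0 and 9.3% at ρ = 0.5. The mixed-model result is not counted here as a further chance.

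**Step 3: what the comparisons estimate.** Let sequence A receive care X then Y, and sequence B receive Y then X. Which of them is the bundle does not matter. Let π₁ and π₂ be the period effects.

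- A(T2) − B(T4) = (π₁ + X) − (π₂ + X) = π₁ − π₂
- A(T4) − B(T2) = (π₂ + Y) − (π₁ + Y) = π₂ − π₁
- ½[(A(T2) − A(T4)) − (B(T2) − B(T4))] = X − Y

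The treatment effect cancels from both listed pairs. Only the third line, which the plan does not list, isolates it.

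**Step 4: consequence.** Rejection rates from 20,000 simulated trials, 18 per sequence, SD 0.05. Each cell gives ρ = 0, then ρ = 0.5. The period shifts are assumed.

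| True bundle effect | Period shift | Each listed pair | Either pair | Crossover contrast |
|---|---|---|---|---|
| 0.04 | 0 | 5%, 5% | 9.7%, 8.9% | 91.1%, 99.7% |
| 0 | 0.02 | 21–22%, 22% | 38.1%, 41.9% | 4.9%, 5.0% |
| 0 | 0.04 | 64%, 65% | 87.2%, 93.7% | 4.9%, 5.2% |

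**The case against.** The best defence is that the plan already ranks its evidence. One endpoint is called primary, it carries the sample size, and everything else is labelled secondary. Leaving secondary outcomes unadjusted under one primary is ordinary practice, and any ordering or exploratory label may sit in an analysis plan that is not shown. All of that stands. A reader might infer that the trial has no hierarchy of outcomes; the documents do not support this.

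A reader might also count every in-hospital test and treat the total as the chance of falsely confirming the hypothesis. Five independent tests give 1 − 0.95⁵ = 22.6%, and ten give 1 − 0.95¹⁰ = 40.1%. These are chances of any significant result, and they depend on assumed correlations and on which tests are counted. The article nowhere says that one significant result confirms the hypothesis. The hypothesis joins sleep, neurodevelopment and growth with an and, and growth is only described at follow-up. If every part had to succeed, the error would be at or below 5%.

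It can further be said that the mixed model may be the deciding analysis, with the pairs only illustrative. That would remove the doubling in Step 2, but the text does not say so. Nor does the model as described settle the matter: intervention is a between-subjects factor there, whereas in this design treatment varies within the infant. If the factor is the allocated group, its main effect compares sequences and the bundle effect cancels again.

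**Conclusion.** The point holds for the primary endpoint. The Data analysis section does not name the test that decides the trial. If either listed comparison may be called significant, the false-positive chance is about 8% to 10%, against the planned 5%. That range rests on an assumed within-infant correlation of 0.8 to 0 and on no period effect; at a correlation of 0.9 it would be about 7%. If both comparisons had to be significant, the rate would be below 5%, but the article states neither rule.

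The larger defect needs no assumption about correlation. Because the groups differ only in order, both listed pairs compare like with like and cannot show a bundle effect. Adjusting their p-values would leave that untouched. The point does not extend to a family-wise error rate for the whole hypothesis, or to a general fault in having unadjusted secondary outcomes.

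**What to change.** In the Data analysis section, replace the two listed pairs with one deciding test: the bundle-versus-standard-care contrast for sleep efficiency, from a mixed model with treatment as a within-infant factor, fixed period and sequence terms and a random infant effect, at two-sided 0.05. This is the kind of contrast that reproduces the stated sample size.

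Report sleep duration, fragmentation index, limb-movement amplitude and the Burdjalov Score with the same contrast and 95% confidence intervals, as supportive results. A formal testing order for them is optional. In the Discussion, tie any claim of efficacy to the primary test.

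The cost is wording, provided that it is settled before the data are analysed; no infants, visits or measurements are added. The small downside is that a secondary p < 0.05 could not be claimed as confirmation if the primary test fails.
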